### Data Management

Because of the eHealth nature of the intervention, all data entry and collection are done online and therefore are programmed to be completely automated. The intervention website is secured with up-to-date online security protocols and certificates safeguarding private information of participants. Users must sign in to get access to their profile and logged data. To sign in, a user name (email address) and password are required. Passwords are stored by using the MD5 hash algorithm. Each user gets their own session after signing in. This session will be killed when the user closes the browser or when the session times out. All data are stored in a MySQL database. To access this database, a password is required that contains digits as well as characters, randomly created. The site uses the HTTPS protocol and is secured by a Comodo SSL Certificate.

Data storage will be extensively tested in the pilot phase. All the participants are assigned an anonymous personal identifier that will be used for all the tables containing data during data collection in the MySQL database. The data will be stored on secure hosting servers for 20 years after the completion of the intervention period.

### Statistical Analyses

#### Intervention Effects

Primary analyses will be unadjusted. Depending on the distribution of continuous, categorical, and interval outcomes, an appropriate distribution and relevant statistical models will be used. These models will assess intervention effects at end-of-intervention (1-year and 2-year) as well as the difference between 1- and 2-year measurements. Baseline characteristics will be compared between groups using *t* tests for continuous variables and chi-square tests for categorical variables. Mann-Whitney tests will be used when baseline data are not normally distributed. If necessary, multivariate analysis, including multi-analysis of variance and multiple regression, will be performed to adjust potential confounders, including baseline demographic and behavioral characteristics. The covariates associated with outcomes or contributing to a significant part of variation of used multivariate models will be adjusted as potential confounders. The final model will include these covariates or remove those that do not affect estimates, if models show evidence of overfitting.

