Alcohol consumption is not an unequivocal area in comparison with the behaviors discussed above. Low to moderate alcohol consumption may very well have positive effects on brain health, but too much alcohol is harmful to the brain. Cross-sectional studies show that moderate alcohol consumption (up to three units a day) may have beneficial effects on episodic memory, executive functioning, and processing speed of the brain [27-30]. However, these results should be interpreted with care. There are no systematic or controlled-trial intervention studies available that examine the influence of alcohol consumption on cognitive functioning, but earlier research has shown that alcohol consumption higher than three units per day is harmful to the brain and can cause Korsakoff’s syndrome [31]. In addition, it is not clear whether the positive effects on cognition are the direct result of the alcohol consumption itself. It may also be that people who have a lifestyle that includes moderate alcohol consumption also moderate themselves in other lifestyle areas, making them better cognitive agers. Further, a recent meta-analysis of epidemiological studies claimed that a reduction of 17% in alcohol consumption causes a 10% reduction in risk of cardiovascular diseases [32].

In a very elaborate review, Goel et al conclude that both acute and chronic sleep deprivation severely influence cognitive capabilities, starting with a measurable drop in performance on executive functioning tasks after being awake for 16 hours [33]. Among others, sleep deprivation further negatively influences psychomotor speed, learning and memory, and working memory performance, and causes faster performance deterioration on longer tasks [33]. Sleep deprivation by lifestyle choice, whether it is chronic or acute, affects executive functioning as the prefrontal and anterior cingulate cortices and posterior parietal systems are especially susceptible to sleep loss [33].

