### Research Questions and Outcome Measures

Our primary research questions are the following: (1) Is successful health behavior change related to better cognitive aging patterns over time? Change scores will be calculated by subtracting baseline scores from scores at year 1 and year 2, (2) Does the BAM facilitate health behavior change? (see Multimedia Appendix 3 for the construction of the overall lifestyle score), and (3) Does the BAM facilitate health behavior change in certain specific lifestyle areas better than others?

Our secondary research questions are as follows: (1) Is there a dose-response relationship between the number of goals participants set and the expected amount of health behavior improvement? and (2) Does the BAM increase feelings of self-efficacy in health-related behavior and a change in self-control scores from baseline to 1 and 2 years of intervention, as measured with the Self-Control Scale [56]. In other words, does the BAM increase feelings of being in control of one’s life?

Our primary outcome measures are (1) cognitive change over time, (2) overall lifestyle change over time, and (3) specific lifestyle changes over time. The secondary outcome measures consist of (1) number of goals set, (2) change in self-efficacy, and (3) change in self-control.

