### Sequence Generation, Allocation Concealment Mechanism, Implementation, and Blinding

This pragmatic field trial does not use a control group. Therefore, sequence generation, allocation concealment, implementation, and blinding are not discussed.

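### Primary question 1 relates self-selected lifestyle change to cognitive change, yet its primary analysis is fixed as unadjusted, with confounders admitted later by a data-driven rule

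*Protocol article*

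**What the plan says.** Research Questions and Outcome Measures puts this question first: "Is successful health behavior change related to better cognitive aging patterns over time". It defines the measure as a raw difference: "Change scores will be calculated by subtracting baseline scores from scores at year 1 and year 2". The abstract also names the relationship between lifestyle change and cognitive aging as the main outcome measure.

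The section on sequence generation and blinding confirms that "This pragmatic field trial does not use a control group". Intervention Effects, under Statistical Analyses, opens with "Primary analyses will be unadjusted". It then allows a conditional second step: "If necessary, multivariate analysis, including multi-analysis of variance and multiple regression, will be performed to adjust potential confounders", with baseline demographic and behavioral characteristics named as the candidate class. Entry works as follows: "The covariates associated with outcomes or contributing to a significant part of variation of used multivariate models will be adjusted as potential confounders". At the last step, the analyst either keeps these covariates or may "remove those that do not affect estimates, if models show evidence of overfitting".

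Secondary Analyses treats the link between number of goals and lifestyle change differently. There a multivariable linear regression with confounder adjustment is planned outright.

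**The concern.** An unadjusted primary analysis is defensible when randomisation balances the groups. Here successful lifestyle change is something participants bring about themselves, so whatever makes a person more likely to change may also shape the cognitive course.

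The article recognises this mechanism. On alcohol, its Introduction warns that "people who have a lifestyle that includes moderate alcohol consumption also moderate themselves in other lifestyle areas, making them better cognitive agers" may be the real explanation. It also reports that smokers decline faster with age, which ties a starting lifestyle characteristic to the cognitive slope.

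The fallback does not close the gap, for three reasons:
- No criterion says when adjustment is necessary.
- Entry never considers association with lifestyle change, so a variable tied strongly to the exposure and modestly to the outcome can be missed.
- The final model depends on the data at hand, so its nominal p-values and intervals cannot be taken at face value.

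Any adjusted result would also rank below the declared unadjusted one. At stake is a positive answer to question 1 that reflects who changed rather than what change did.

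**Working it through.** **The plan's own figure.** Sample Size gives n=166, two-tailed alpha .05, power 0.8, about 20% dropout and a target of 200. Inflating gives 166 × 1.2 = 199.2, which rounds to 200. The 166 cannot be uniquely re-derived, because no baseline rate, SD or test is stated. It was set for a 15% reduction in risk factors, not for question 1. It is not in dispute and serves below only as a plausible analysis size.

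**Inputs.** n=166 and two-sided 5% come from the article. The correlations of a confounder with lifestyle change (a) and with cognitive change (b) are assumptions, because the documents give none.

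**Confounding.** Suppose there is no true effect and one confounder is omitted.
- Spurious correlation between the two changes: r = a × b.
- Mean of the Fisher z test: m = √(n − 3) × atanh(r), with √163 = 12.767.
- False-positive rate: 1 − Φ(1.96 − m) + Φ(−1.96 − m).

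| a, b | r | m | false-positive rate |
|---|---|---|---|
| 0.1, 0.1 | 0.01 | 0.128 | 5.2% |
| 0.2, 0.2 | 0.04 | 0.511 | 8.0% |
| 0.3, 0.3 | 0.09 | 1.152 | 21% |
| 0.3, 0.4 | 0.12 | 1.539 | 34% |
| 0.4, 0.4 | 0.16 | 2.060 | 54% |

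Correct adjustment for that confounder returns the rate to 5%.

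**Should the baseline scores go into the primary model?** I simulated n=166 with no true change in anyone, independent measurement errors and 6,000 repetitions per setting. Model A is the unadjusted test of change against change. Model B regresses follow-up cognition on lifestyle change plus baseline cognition and baseline lifestyle. False-positive rates:

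| correlation of true lifestyle and true cognition | reliability | Model A | Model B |
|---|---|---|---|
| 0 | 0.6 / 0.7 / 0.8 | 5.4 / 4.5 / 5.3% | 5.5 / 4.9 / 5.3% |
| 0.3 | 0.6 / 0.7 / 0.8 | 5.2 / 4.6 / 5.3% | 9.2 / 7.7 / 6.7% |
| 0.5 | 0.6 / 0.7 / 0.8 | 4.6 / 5.1 / 5.0% | 19 / 16 / 11% |

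Measurement error alone does not inflate the change-on-change test. Adjusting for error-prone baselines can inflate it when the underlying traits are correlated.

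**The case against.** Several points on the other side stand.

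- Weak confounding does little harm: at 0.1 and 0.1 the error rate barely moves. Nothing in the documents shows that age, within the 40 to 67 range, correlates as strongly as 0.3 with both changes.
- Change scores already remove stable differences in level between people.
- The question asks only whether the changes are related, and an unadjusted correlation does describe that.
- The candidate covariates are named as a class in advance, and removal applies only where overfitting is evident. Calling the rule pure significance testing would be unfair.
- The opening sentence also covers questions 2 and 3, which concern lifestyle change within the same people. An unadjusted estimate is natural there.

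These points limit the size and scope of the problem, but they do not justify the choice for question 1. The Objective and Introduction ask whether behavior change results in healthier cognitive aging, so a bare correlation will be read causally.

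A reader might also infer that regression to the mean distorts the change-on-change association. The documents do not support that. With independent errors the test holds its 5% level. Bias would need correlated baseline errors, or baseline lifestyle driving both changes. The Introduction makes the second plausible, but nothing in the article establishes or sizes either. Nor does the article plan an analysis of participants selected for low baseline scores, where such an effect would show directly.

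**Conclusion.** The point holds for primary question 1. The article makes a stated choice that suits a randomised comparison and applies it to an observational association, while adjusting a secondary association of the same kind. This is not detail left to an analysis plan, since a consistent plan would carry the unadjusted choice forward.

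The size is conditional. It runs from negligible to a false-positive rate of about 54% at n=166, for assumed confounder correlations from 0.1 to 0.4 with both changes. It rests on one omitted confounder, no true effect and a test of correlation.

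Two stronger conclusions are not supported. It is not shown that the answer to question 1 will be wrong, because the actual correlations are unknown. Nor would an adjusted model give a causal answer, because change is self-selected and there is no control group.

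**What to change.** For question 1 only:

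1. Make the primary model a regression of cognitive change on lifestyle change, adjusted for confounders fixed in advance on subject-matter grounds from intake data: age, sex and, if the individual-characteristics questionnaire records it, education.
2. Report the unadjusted estimate alongside as supportive.
3. Remove the data-driven entry and removal rule for this model.
4. Pre-specify, as sensitivity analyses, models that add baseline BAM-COG and baseline lifestyle score, and state that error in these scores can bias the result.
5. Word the conclusion as an association.

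State that questions 2 and 3 remain unadjusted within-person comparisons.

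The cost is a change of wording in the protocol and in any analysis plan, a little more analysis and a few degrees of freedom. Baseline lifestyle, individual characteristics and BAM-COG are already collected, so no new data are needed. If education is not recorded, it drops out of the set.

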**Objective:**

This study aims to answer two questions: (1) Is the use of a self-motivated, complex eHealth intervention effective in changing multiple health behaviors related to cognitive aging in Dutch adults in the work force, especially those aged 40 and over? and (2) Does this health behavior change result in healthier cognitive aging patterns and contribute to preventing or delaying future onset of neurodegenerative syndromes?

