### Study Design

For this study, we will use a quasi-experimental longitudinal pre-posttest design, with measurements at baseline and after 12 and 24 months. Only Dutch individuals within the Netherlands will be recruited. The intervention website is programmed in Dutch and as such will not be feasible for implementation outside the Netherlands. Since the Brain Aging Monitor is an eHealth intervention and the Netherlands has an Internet penetration of 94% of all households [41], there is no limit to its potential reach within the Dutch-speaking community. There are no regional restrictions that keep uptake of the intervention pinned to the region of the research institute. Since the entire intervention is based on self-management, contact with the research team is strictly limited to technical support. Considering the fact that the protocol relates to a pragmatic field study that will recruit both at an individual and organizational level, we cannot give an accurate estimate of the number of sites needed to obtain the necessary number of participants. For a sample size calculation, we refer to the description of sample size (Nederlands Trial Register: NTR4144).

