#### Secondary Analyses

Total set goals and specific lifestyle area goals will be reported descriptively. The changes of lifestyle within the goal setting group will be reported in absolute difference at end of intervention. The dose-response association between goals and change of lifestyle will be analyzed by multivariable linear regression model, and potential confounders will be adjusted. The change in self-efficacy and self-control scores will be reported in absolute difference at the end of the intervention. The association between the use of BAM and increased feelings of self-efficacy or self-control will be analyzed by multivariate analysis.

Analysis will be performed per protocol. The dropout in this pragmatic field study is likely to be high but can be considered a separate outcome for the implementation and feasibility of these types of intervention. As such, it represents valuable data about the quasi-experimental study design.

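### The analysis section plans between-group tests and speaks of intervention effects, but the study is one uncontrolled pre-post cohort, so it can report change among users and associations, not effectiveness or prevention

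*Protocol article*

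**What the plan says.** All references are to the protocol article.

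- **Design.** Study Design: "we will use a quasi-experimental longitudinal pre-posttest design, with measurements at baseline and after 12 and 24 months". The section on sequence generation, allocation and blinding: "This pragmatic field trial does not use a control group".
- **Primary analysis.** Under Intervention Effects, the primary analyses are unadjusted, and "These models will assess intervention effects at end-of-intervention (1-year and 2-year"), together with the difference between those two time points. Further on, "Baseline characteristics will be compared between groups" by t and chi-square tests, and "Mann-Whitney tests will be used when baseline data are not normally distributed".
- **Secondary analysis.** "The association between the use of BAM and increased feelings of self-efficacy or self-control will be analyzed by multivariate analysis". The same section says that analysis is per protocol and that dropout will probably be high.
- **Questions and outcomes.** The Abstract's Objective asks whether the intervention is effective. It also asks whether the behaviour change leads to healthier cognitive aging and will "contribute to preventing or delaying future onset of neurodegenerative syndromes". Research Questions and Outcome Measures asks whether the BAM facilitates behaviour change, and whether successful change is related to cognitive aging. It lists cognitive change, overall lifestyle change and specific lifestyle changes as primary outcomes.

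**The concern.** The t (as used here), chi-square and Mann-Whitney tests compare independent samples. A cohort in which everyone is offered the same programme does not supply such samples unless the plan says how to divide it, and the plan does not. This goes beyond detail that an analysis plan would fill in, because the text specifies a comparison that the stated design does not define.

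The label is the larger problem. If the plan is followed as written, the mean change among people who return will be reported as an intervention effect and read as a yes or no on effectiveness. That credits or charges the BAM with change that the design cannot attribute to it. A reader of the objective could also take a two-year change in game scores as evidence about the onset of neurodegenerative disease.

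**Working it through.** No figure in the plan bears on this point, so the check sets the statements side by side.

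**1. Which groups?** The tests need at least two defined groups. The only group named in the analysis text is the goal-setting group (Secondary Analyses), and only change within it is to be reported. Other divisions could be made from the article: two recruitment streams of about 50% each (Recruitment), participants under 40 versus 40 and over (Principal Considerations, Eligibility Criteria), or returners versus non-returners. None is linked to the baseline tests. All are self-selected or demographic splits, so none would give an intervention effect.

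**2. What does use of the BAM contrast?** Use does vary. Participants choose how many goals to set, and people who unsubscribe may agree to come back for follow-up without setting goals (Intervention, Data Collection Methods). The association can therefore be estimated once use is defined, but the article does not define it for self-efficacy and self-control. For lifestyle change it already does: the dose is the number of goals set.

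**3. What does the one-group change contain?** For people who return,

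mean observed change = BAM effect + retest learning + ageing and secular change + change that motivated volunteers would have made anyway + outside programmes not prompted by the BAM + selective retention.

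This is one observed quantity with several unknown terms. The article itself gives grounds for most of them:

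- Retest learning (cognitive outcome only): the BAM-COG is presented again at 365 and 730 days (Participant Timeline), so it is taken three times.
- Motivation: most participants are expected to be already in the preparation, action or maintenance stage (Use of Health Behavior Change Theory).
- Outside programmes: concomitant care is said to be hard to control (Intervention). The article counts help that the BAM prompts as part of its aim, but cannot separate it from help sought independently.
- Retention: the analysis is per protocol and dropout is expected to be high (Secondary Analyses).

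In a controlled design, the terms common to both arms would cancel in the difference. Here nothing cancels. The optional adjustment for baseline covariates does not help, because it does not show what the same people would have done without the BAM.

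**4. Which questions survive as worded?**

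| Question | Can the data answer it as worded? |
|---|---|
| Is successful behaviour change related to cognitive aging? (Research Questions) | Yes, as an association |
| Is there a dose-response between goals set and lifestyle change? | Yes, as an adjusted association |
| Does the BAM facilitate behaviour change, overall or in some areas more than others? | No, only whether users changed |
| Is the intervention effective? (Abstract, Introduction) | No |
| Does the change contribute to preventing or delaying neurodegenerative syndromes? (Abstract; softened in the Introduction) | No, as no disease outcome is listed |

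**The case against.** The uncontrolled design is declared openly, and Principal Considerations gives reasons: randomisation was impractical, a stepped-wedge design did not fit the two-year period, and organisations were unlikely to accept a control role. The disputed tests concern baseline characteristics only, not the outcomes. Research Questions and Outcome Measures already defines within-person change scores, and the exact model may properly be left to an analysis plan. The first primary question is worded as an association, and no planned analysis claims to test disease onset.

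Much of this stands. The lack of a comparator is a declared limitation, not an error, and insisting on a mixed model would be partly preference. But explaining why there is no control group does not license effect wording. The Conclusion still promises evidence on effectiveness.

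Three stronger readings are tempting and are not supported:

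- *Use of the BAM has no variation, so the association cannot be estimated.* Goal numbers are free and unsubscribers may return for follow-up, so use varies. It is only undefined.
- *Artefacts alone would produce a positive answer.* Ageing may offset retest gains, and the net sign is unknown. They could do so; the documents do not show that they would.
- *Regression to the mean is as large as the effect the trial is sized for.* Eligibility does not select on baseline score, so this mechanism has no expected shift in the whole cohort from the entry criteria. A shift in a low-scoring subgroup would be in SDs of the score, which is not comparable with a detectable change in SDs of change. The article gives no reliability or retest figure, and the sample size rests on a 15% reduction in risk factors, not on a standardised change.

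**Conclusion.** The point holds. The analysis section specifies between-group baseline tests without groups and an exposure contrast without a definition. It also calls an unadjusted one-group change an intervention effect. The within-person changes, the association between lifestyle and cognitive change, and the goals dose-response can all be analysed. The effectiveness questions cannot be answered as worded, and the prevention wording does not match the listed outcomes.

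No numerical size is claimed, because the documents do not support one. What changes is the kind of conclusion the study can draw. The verdict rests on the article's own statements about design, outcomes and analysis. It also assumes that the per-protocol statement, which sits under Secondary Analyses, applies to the primary outcomes too. If it does not, selective retention remains a concern through dropout, and the rest is unaffected.

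**What to change.** 1. **Groups and method.** Delete the between-group baseline tests, or restrict them to named contrasts on data already collected. Returners versus non-returners at 12 and 24 months is the most useful, because it bears on selective retention. State that the change scores will be analysed with a paired or repeated-measures method.
2. **Use of the BAM.** For self-efficacy and self-control, define use as a dose, for example the number of goals set, as is already planned for lifestyle change.
3. **Wording.** Replace intervention effects, and the questions on effectiveness and facilitation, with within-person change among users and association. Align the objective in the Abstract and Introduction with the cognitive and lifestyle outcomes actually listed, and leave prevention or delay of disease as background motivation.

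Because enrolment stays open, follow-up scores could also be set against the baseline scores of later registrants. This is exploratory at most: it compares people who stayed with everyone who newly registers, so survivor selection must be stated as a limitation, along with possible differences in who registers later.

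The main changes need only revised protocol and analysis wording, with no new data collection. The price is weaker causal language in the eventual report.
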